**Appendix 5**

# Table 4 Depression Anxiety and Stress Scale(DASS-21)

Number： Name：

ID： Tel：

(The subscale scores were multiplied by 2 to give a score for that subscale, with higher scores representing more of that emotion.)

| Please read each statement and indicate the extent to which it applies to you in the past week by checking the appropriate box. There are no right or wrong answers. Do not spend too much time on any statement.The scoring criteria are as follows: 0 Does not apply to me at all 1 Applies to me to some extent, or applies sometimes 2 Applies to me to a onsiderable extent, or applies most of the time 3 Applies to me very much, or applies most of the time | | | | | | | | | | | |
| --- | --- | --- | --- | --- | --- | --- | --- | --- | --- | --- | --- |
|  |  | | | | 0 | 1 | | 2 | | 3 | score |
| 1 | I couldn’t seem to experience any positive feeling at all | | | |  |  | |  | |  |  |
| 2 | I found it difficult to work up the initiative to do things | | | |  |  | |  | |  |  |
| 3 | I felt that I had nothing to look forward to | | | |  |  | |  | |  |  |
| 4 | I felt down-hearted and blue | | | |  |  | |  | |  |  |
| 5 | I was unable to become enthusiastic about anything | | | |  |  | |  | |  |  |
| 6 | I felt I wasn’t worth much as a person | | | |  |  | |  | |  |  |
| 7 | I felt that life was meaningless | | | |  |  | |  | |  |  |
| Depression Scale | | | | | | | | Total score | | |  |
| 8 | I was aware of dryness of my mouth | | | |  |  | |  | |  |  |
| 9 | I experienced breathing difficulty (e.g. excessively rapid breathing, breathlessness in the absence of physical exertion) | | | |  |  | |  | |  |  |
| 10 | I experienced trembling (e.g. in the hands) | | | |  |  | |  | |  |  |
| 11 | I was worried about situations in which I might panic and make a fool of myself | | | |  |  | |  | |  |  |
| 12 | I felt I was close to panic | | | |  |  | |  | |  |  |
| 13 | I was aware of the action of my heart in the absence of physical  exertion (e.g. sense of heart rate increase, heart missing a beat) | | | |  |  | |  | |  |  |
| 14 | I felt scared without any good reason | | | |  |  | |  | |  |  |
| Anxiety Scale | | | | | | | | Total score | | |  |
| 15 | I found it difficult to relax | | | |  |  | |  | |  |  |
| 16 | I tended to over-react to situations | | | |  |  | |  | |  |  |
| 17 | I felt that I was using a lot of nervous energy | | | |  |  | |  | |  |  |
| 18 | I felt that I was rather touchy | | | |  |  | |  | |  |  |
| 19 | I found it hard to wind down | | | |  |  | |  | |  |  |
| 20 | I was intolerant of anything that kept me from getting on with what I  was doing | | | |  |  | |  | |  |  |
| 21 | I found myself getting agitated | | | |  |  | |  | |  |  |
| Stress Scale | | | | | | | | Total score | | |  |
| Recommended cut-off scores for conventional severity labels (normal, moderate, severe) are as follows: NB Scores on the DASS-21 will need to be multiplied by 2 to calculate the final score. | | | | | | | | | | | |
|  | | Normal | Mild | Moderate | | | Severe | | Extremely Severe | | |
| Depression | | 0-9 | 10-13 | 14-20 | | | 21-27 | | 28+ | | |
| Anxiety | | 0-7 | 8-9 | 10-14 | | | 15-19 | | 20+ | | |
| Stress | | 0-14 | 15-18 | 19-25 | | | 26-33 | | 34+ | | |
| Lovibond, S.H. & Lovibond, P.F. (1995). Manual for the Depression Anxiety & Stress Scales. (2nd Ed.)Sydney: Psychology Foundation. | | | | | | | | | | | |

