8.1 Main Efficacy Indicator: Pain Score

(1) Pelvic Pain Rating Scale (for women): It includes the patient's basic information, detailed changes in symptoms, and the effectiveness of previous treatments. It uses pain exacerbated and relieved by sexual activity and menstruation as the starting point for medical history inquiries. Additional details include symptoms related to exercise, urinary, and bowel function.

(2) NIH-CPSI (for men): It mainly consists of three parts, assessing pain or discomfort caused by chronic prostatitis, urinary symptoms, and the impact on quality of life, with a total of nine questions. It is characterized by objectivity and convenience, is quickly accepted by patients, and can provide important references for research and clinical work.

8.2 Secondary Efficacy Indicators:

(1) Anxiety and Depression Scores (DASS-21): For depression, the cutoff values for mild, moderate, and severe depression are 10, 14, and 21, respectively; for the anxiety scale, the cutoff values for mild, moderate, and severe anxiety are 8, 10, and 15, respectively; for the stress scale, the cutoff values for mild, moderate, and severe stress are 15, 19, and 26, respectively.

(2) Surface Electromyography of the Pelvic Floor Muscles: Participants will lie in a supine position, with their upper and lower bodies forming an angle of approximately 120°, and their feet naturally rotated outward. An electrode will be placed in the rectum to collect surface electromyography data from the pelvic floor muscles, while abdominal electrodes will monitor abdominal muscle activity. Before the examination, participants will be instructed to urinate and defecate, taught how to properly contract and relax the pelvic floor muscles, and informed about the assessment process. They will learn how to quickly contract and hold the contraction for 10 seconds. Participants will contract and relax their pelvic floor muscles based on verbal prompts to record surface electromyography values.

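### On the DASS-21 form in Appendix 5, answers 2 and 3 carry the same frequency anchor, which adds avoidable noise to a secondary outcome

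*Protocol*

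**What the plan says.** Appendix 5, Table 4 of the protocol prints the DASS-21 with a four-point response key. The three non-zero options are:

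- Answer 1: "1 Applies to me to some extent, or applies sometimes"
- Answer 2: "2 Applies to me to a onsiderable extent, or applies most of the time"
- Answer 3: "3 Applies to me very much, or applies most of the time"

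The 21 items form three subscales of seven: depression (items 1–7), anxiety (8–14) and stress (15–21). The form states the doubling rule twice, above the items ("The subscale scores were multiplied by 2 to give a score for that subscale") and beside the severity bands ("Scores on the DASS-21 will need to be multiplied by 2 to calculate the final score").

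Section 8.2 names the DASS-21 as a secondary efficacy indicator and lists severity thresholds; for depression, "the cutoff values for mild, moderate, and severe depression are 10, 14, and 21, respectively". These agree with the bands in Appendix 5. The schedule in Appendix 2 has the scale completed at all six time points, t0 to t5.

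**The concern.** Each option joins an intensity clause and a frequency clause with the word *or*, so meeting either clause is enough to choose it. Answer 1 has a frequency clause of its own, which shows that the key is meant to rise in frequency as well as in intensity. Between 2 and 3 the frequency clause does not rise. A symptom present most of the time satisfies both answers, and nothing in the protocol tells the patient or the assessor how to choose.

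The same patient in the same state could thus tick 2 at one visit and 3 at the next. That variation would enter the DASS-21 scores, and comparing dual-target with peripheral stimulation on psychological scores is a stated objective (Section 2). With 22 patients planned per group, avoidable measurement error is worth removing.

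**Working it through.** **Inputs.** All come from Appendix 5, and the Section 8.2 cut-offs agree with them.

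- Items per subscale: 7
- Difference between the two ambiguous answers: 3 − 2 = 1
- Multiplier: 2
- Subscale range: 0 to 7 × 3 × 2 = 42
- Bands used below:

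| Subscale | Moderate | Severe | Extremely severe |
|---|---|---|---|
| Depression | 14–20 | 21–27 | 28+ |
| Anxiety | 10–14 | 15–19 | 20+ |
| Stress | 19–25 | 26–33 | 34+ |

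**Shift from wording alone.** For k ambiguous items, shift = k × 1 × 2.

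- One item: 1 × 1 × 2 = 2 points
- Three items: 3 × 1 × 2 = 6 points
- All seven items: 7 × 1 × 2 = 14 points, that is (7 × 2) × 2 = 28 against (7 × 3) × 2 = 42

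**Crossing a cut-off.**

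- Depression, three ambiguous items, with the other four items summing to 3: scored as 2, (6 + 3) × 2 = 18, moderate; scored as 3, (9 + 3) × 2 = 24, severe.
- Anxiety, three ambiguous items, with the other four summing to 1: (6 + 1) × 2 = 14, moderate, against (9 + 1) × 2 = 20, extremely severe.
- One item is enough at a boundary: depression 20 to 22, anxiety 14 to 16 and stress 24 to 26 each move from moderate to severe.

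**At the ceiling.** Going from 28 to 42 leaves depression and anxiety in the extremely severe band at both ends. Only stress changes, from severe to extremely severe. For depression and anxiety, band changes therefore come from the smaller shifts, not from the 14-point extreme.

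**With distinct anchors.** A key whose frequency clauses differ would bring the shift due to this wording to zero.

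**The case against.** The strongest reply is that only half of each anchor is duplicated. The intensity clauses of answers 2 and 3 differ and are in order, the options are numbered 0 to 3, and the instruction asks how far each statement applies. A patient who answers by intensity is not affected. This stands, and it limits the point to patients who answer by frequency. It does not remove the point, because the *or* makes the frequency clause sufficient by itself.

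The second reply is that the appendix may be an English rendering of the form in use; the same key contains a misspelling in answer 2. This also stands. The documents do not show whether the patients' form repeats the clause. The protocol text still needs correcting in either case.

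Four stronger readings are tempting, and the documents do not support them:

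- *That the comparison is biased.* All arms use the same form, and Section 14.4 assigns the scales to one evaluator. Nothing suggests that the choice between 2 and 3 would differ by arm.
- *That severity classification as an outcome is compromised.* Sections 8.2 and Appendix 5 list the cut-offs as part of the scale's description. Section 11.2.2 describes continuous data by mean and standard deviation and names no analysis by band. The band changes illustrate the size of the shift; they do not show an analysis going wrong.
- *That the psychological evidence rests on this scale alone.* The SF-36, also secondary, includes mental health and role-emotional domains. The DASS-21 is the main dedicated measure of depression, anxiety and stress, not the only psychological outcome.
- *That most answers will fall in the affected range because entry requires an anxiety or depressive disorder.* There is no DASS-21 entry threshold, the form in Appendix 7 allows mild cases, and severe mental illness is excluded.

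Staff training (Section 14.2) promises uniform judgment criteria but gives no rule for choosing between these two answers.

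**Conclusion.** The response key is wrong as printed: answers 2 and 3 share one frequency anchor, and no other part of the protocol separates them. The size is 2 points per affected item after doubling, with a theoretical ceiling of 14 of 42 per subscale. The ceiling requires all seven items to be ambiguous and all to be resolved the same way. One to three items are enough to cross a listed cut-off.

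The consequence is non-differential noise on a secondary outcome. Its amount cannot be calculated, because the documents do not say how many patients answer by frequency or how their answers are distributed. The primary endpoint is untouched. The practical effect rests on one assumption, that the form patients complete carries the same duplicate; if it does not, the error is confined to the appendix. The correction is worth making because it is cheap and the instrument is used at every visit.

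**What to change.** 1. Compare the form patients complete with Appendix 5.
2. If the patient form has the duplicated clause, correct it so that the four options have distinct, ordered frequency anchors, taken from the source instrument and not newly drafted, and correct Appendix 5 to match. If the patient form is already right, correct Appendix 5 only.
3. If affected forms are already in use, keep each patient on one form version from baseline to t5, record the version, and report DASS-21 results by version as a sensitivity check. Do not exclude patients who used the affected form. Recruitment was planned from January 2024, so exclusion could leave few or no data. Changing the form partway through a patient's visits would mix versions within that patient's change scores.

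The cost is one line on a form, some version control and, only if affected forms have been used, one extra sensitivity analysis. With 66 patients split by version and arm, that analysis will be descriptive.

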**Appendix 6**

# Table 5 36-Item Short Form Survey

Number： Name：

ID： Tel：

There are a total of 36 questions below, and after each question, there are several answers to choose from. Please fill in the corresponding score in the score column of the table for the answers you think are appropriate.

| Item |  | | | | |  | | | | | |  | | | | | |  | | | | |  | | | Score |
| --- | --- | --- | --- | --- | --- | --- | --- | --- | --- | --- | --- | --- | --- | --- | --- | --- | --- | --- | --- | --- | --- | --- | --- | --- | --- | --- |
| 1. In general, would you say your health is | Excellent | | | | | Very good | | | | | | Good | | | | | | Fair | | | | | Poor | | |  |
|  | 5 | | | | | 4.4 | | | | | | 3.4 | | | | | | 2 | | | | | 1 | | |  |
| 1. **Compared to one year ago**, how would you rate your health in genera **now**? | Much better | | | | | Somewhat better | | | | | | About the same | | | | | | Somewhat worse | | | | | Much worse | | |  |
|  | 1 | | | | | 2 | | | | | | 3 | | | | | | 4 | | | | | 5 | | |  |
| The following items are about activities you might do during a typical day. Does **your health now limit you** in these activities? If so, how much? | | | | | | | | | | | | Yes, limited a lot | | | | Yes, limited a little | | | | | | No, not limited at all | | | |  |
| 1. **Vigorous activities**, such as running, lifting heavy objects, participating in strenuous sports | | | | | | | | | | | | 1 | | | | 2 | | | | | | 3 | | | |  |
| 1. **Moderate activities**, such as moving a table, pushing a vacuum cleaner, bowling, or playing golf | | | | | | | | | | | | 1 | | | | 2 | | | | | | 3 | | | |  |
| 1. Lifting or carrying groceries | | | | | | | | | | | | 1 | | | | 2 | | | | | | 3 | | | |  |
| 1. Climbing **several** flights of stairs | | | | | | | | | | | | 1 | | | | 2 | | | | | | 3 | | | |  |
| 1. Climbing **one** flight of stairs | | | | | | | | | | | | 1 | | | | 2 | | | | | | 3 | | | |  |
| 1. Bending, kneeling, or stooping | | | | | | | | | | | | 1 | | | | 2 | | | | | | 3 | | | |  |
| 1. Walking **more than a mile** | | | | | | | | | | | | 1 | | | | 2 | | | | | | 3 | | | |  |
| 1. Walking **several blocks** | | | | | | | | | | | | 1 | | | | 2 | | | | | | 3 | | | |  |
| 1. Walking **one block** | | | | | | | | | | | | 1 | | | | 2 | | | | | | 3 | | | |  |
| 1. Bathing or dressing yourself | | | | | | | | | | | | 1 | | | | 2 | | | | | | 3 | | | |  |
| During the **past 4 weeks**, have you had any of the following problems with your work or other regular daily activities **as a result of your physical health**? | | | | | | | | | | | | | | | | | | | No | | | | Yes | | |  |
| 1. Cut down the **amount of time** you spent on work or other activities | | | | | | | | | | | | | | | | | | | 1 | | | | 2 | | |  |
| 1. **Accomplished less** than you would like | | | | | | | | | | | | | | | | | | | 1 | | | | 2 | | |  |
| 1. Were limited in the **kind** of work or other activities | | | | | | | | | | | | | | | | | | | 1 | | | | 2 | | |  |
| 1. Had **difficulty** performing the work or other activities (for example, it took extra effort) | | | | | | | | | | | | | | | | | | | 1 | | | | 2 | | |  |
| During the **past 4 weeks**, have you had any of the following problems with your work or other regular daily activities **as a result of any emotional problems** (such as feeling depressed or anxious)? | | | | | | | | | | | | | | | | | | | No | | | | Yes | | |  |
| 1. Cut down the **amount of time** you spent on work or other activities | | | | | | | | | | | | | | | | | | | 1 | | | | 2 | | |  |
| 1. **Accomplished less** than you would like | | | | | | | | | | | | | | | | | | | 1 | | | | 2 | | |  |
| 19. Didn't do work or other activities as **carefully** as usual | | | | | | | | | | | | | | | | | | | 1 | | | | 2 | | |  |
| 20. During the **past 4 weeks**, to what extent has your physical health or emotional problems interfered with your normal social activities with family, friends, neighbors, or groups? | | | | | Not at all | | | | | Slightly | | | | | Moderately | | | | Quite a bit | | | | Extremely | | |  |
|  |  |  |  |  | 5 | | | | | 4 | | | | | 3 | | | | 2 | | | | 1 | | |  |
| 21.How much **bodily** pain have you had during the **past 4 weeks**? | None | | | Very mild | | | | | | Mild | | | | | Moderate | | | | | Severe | | | | Very severe | |  |
|  | 6 | | | 5.4 | | | | | | 4.2 | | | | | 3.1 | | | | | 2.2 | | | | 1 | |  |
| 22.During the past 4 weeks, how much did pain interfere with your normal work (including both work outside the home and housework)? | | Score selection | | | | | Not at all | | | | A little bit | | | | Moderately | | | | Quite a bit | | | | Extremely | | |  |
|  |  | Answered items 21 | | | | | 6 | | | | 4.75 | | | | 3.5 | | | | 2.25 | | | | 1 | | |  |
|  |  | Unanswered items 21 | | | | | 5 | | | | 4 | | | | 3 | | | | 2 | | | | 1 | | |  |
| These questions are about how you feel and how things have been with you during the past 4 weeks. For each question, please give the one answer that comes closest to the way you have been feeling. How much of the time during the past 4 weeks... | | | | All of the time | | | | | Most of the time | | | | A good bit of the time | | | | Some of the time | | | | A little of the time | | | | None of the time |  |
| 23.Did you feel full of pep? | | | | 6 | | | | | 5 | | | | 4 | | | | 3 | | | | 2 | | | | 1 |  |
| 24.Have you been a very nervous person? | | | | 1 | | | | | 2 | | | | 3 | | | | 4 | | | | 5 | | | | 6 |  |
| 25.Have you felt so down in the dumps that nothing could cheer you up? | | | | 1 | | | | | 2 | | | | 3 | | | | 4 | | | | 5 | | | | 6 |  |
| 26.Have you felt calm and peaceful? | | | | 6 | | | | | 5 | | | | 4 | | | | 3 | | | | 2 | | | | 1 |  |
| 27.Did you have a lot of energy? | | | | 6 | | | | | 5 | | | | 4 | | | | 3 | | | | 2 | | | | 1 |  |
| 28.Have you felt down hearted and blue? | | | | 1 | | | | | 2 | | | | 3 | | | | 4 | | | | 5 | | | | 6 |  |
| 29.Did you feel worn out? | | | | 1 | | | | | 2 | | | | 3 | | | | 4 | | | | 5 | | | | 6 |  |
| 30.Have you been a happy person? | | | | 6 | | | | | 5 | | | | 4 | | | | 3 | | | | 2 | | | | 1 |  |
| 31.Did you feel tired? | | | | 1 | | | | | 2 | | | | 3 | | | | 4 | | | | 5 | | | | 6 |  |
| 32.During the **past 4 weeks**, how much of the time has **your physical health or emotional problems** interfered with your social activities (like visiting with friends, relatives, etc.)? | | | All of the time | | | | | Most of the time | | | | | | Some of the time | | | | | A little of the time | | | | | None of the time | |  |
|  |  |  | 1 | | | | | 2 | | | | | | 3 | | | | | 4 | | | | | 5 | |  |
| How TRUE or FALSE is **each** of the following statements for you. | | | Definitely true | | | | | Mostly true | | | | | | Don't know | | | | | Mostly false | | | | | Definitely false | |  |
| 1. I seem to get sick a little easier than other people | | | 1 | | | | | 2 | | | | | | 3 | | | | | 4 | | | | | 5 | |  |
| 1. I am as healthy as anybody I know | | | 5 | | | | | 4 | | | | | | 3 | | | | | 2 | | | | | 1 | |  |
| 1. I expect my health to get worse | | | 1 | | | | | 2 | | | | | | 3 | | | | | 4 | | | | | 5 | |  |
| 1. My health is excellent | | | 5 | | | | | 4 | | | | | | 3 | | | | | 2 | | | | | 1 | |  |
| Score conversion = (actual score - lowest score in that aspect) / (highest score in that aspect - lowest score in that aspect) × 100; missing entry scores are replaced by the average score of their respective aspect. | | | | | | | | | | | | | | | | | | | conversion formula | | | | | | | Score conversion |
| Physical Functioning(PF), Consist of items 3-12, | | | | | | | | | | | | | | | | | | | PF=(actual score-10）/20×100 | | | | | | |  |
| Role-Physical(RP) ,Consist of items 13-16, | | | | | | | | | | | | | | | | | | | RP=（actual score-4）/4×100 | | | | | | |  |
| Bodily Pain(BP), Consist of items 21, 22, | | | | | | | | | | | | | | | | | | | BP=（actual score-2）/10×100 | | | | | | |  |
| General Health(GH), Consist of items 1, 33-36, | | | | | | | | | | | | | | | | | | | GH=（actual score-5）/20×100 | | | | | | |  |
| Vitality(VT), Consist of items 23, 27, 29, 31, | | | | | | | | | | | | | | | | | | | VT=（actual score-4）/20×100 | | | | | | |  |
| Social Functioning(SF), Consist of items 20, 32, | | | | | | | | | | | | | | | | | | | SF=（actual score-2）/9×100 | | | | | | |  |
| Role-Emotional(RE), Consist of items 17-19, | | | | | | | | | | | | | | | | | | | RE=（actual score-3）/3×100 | | | | | | |  |
| Mental Health(MH), Consist of items 24-26, 28, 30, | | | | | | | | | | | | | | | | | | | MH=（actual score-5）/25×10 | | | | | | |  |
| Reported Health Transition(HT), Consist of items 2, | | | | | | | | | | | | | | | | | | | HT=（actual score-1）/4×100 | | | | | | |  |
| ReferencesWare, J.E., Jr., & Sherbourne, C.D. “The MOS 36-Item Short-Form Health Survey (SF-36): I. Conceptual Framework and Item Selection,”. Medical Care, 30:473-483, 1992.Hays, R.D., & Shapiro, M.F. “An Overview of Generic Health-Related Quality of Life Measures for HIV Research,” Quality of Life Research. 1:91-97, 1992. Steward, A.L., Sherbourne, C., Hayes, R.D., et al. “Summary and Discussion of MOS Measures,” in A.L. Stewart & J.E. Ware (eds.), Measuring Functioning and Well-Being: The Medical Outcome Study Approach (pp. 345-371). Durham, NC: Duke University Press, 1992. | | | | | | | | | | | | | | | | | | | | | | | | | | |

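### The SF-36 sheet scores both role domains in the opposite direction to the other six, and its Social Functioning and Mental Health formulas break the sheet's own 0–100 rule

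*Protocol*

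**What the plan says.** The Plan Summary and section 8.2 list SF-36 among the secondary efficacy indicators, and section 2 makes quality of life one of the things to be compared. Appendix 2 schedules the scale at all six time points, t0 to t5.

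Appendix 6 (Table 5) is the form itself, with item codes and scoring. Its general rule is "actual score - lowest score in that aspect) / (highest score in that aspect - lowest score in that aspect) × 100", which puts every domain on 0 to 100. The table then prints one formula per domain:

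- Role-Physical (items 13–16): "RP=（actual score-4）/4×100"
- Role-Emotional (items 17–19): "RE=（actual score-3）/3×100"
- Social Functioning (items 20 and 32): "SF=（actual score-2）/9×100"
- Mental Health (items 24–26, 28, 30): "MH=（actual score-5）/25×10"

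The stem for items 13–16 and the stem for items 17–19 both ask "have you had any of the following problems with your work or other regular daily activities". All seven items are coded No = 1, Yes = 2.

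Item 20 asks "to what extent has your physical health or emotional problems interfered with your normal social activities" and is coded from 5 (not at all) to 1 (extremely). Item 32 asks how often such problems "interfered with your social activities (like visiting with friends, relatives, etc" and is coded from 1 (all of the time) to 5 (none of the time).

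**The concern.** There are two separate faults.

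The first is direction. On the role items a Yes reports a problem, and Yes carries the larger code. Nothing in the sheet reverses it before conversion, so more limitation gives a higher Role-Physical or Role-Emotional score. On the other six domains the larger code goes with better health. Anyone reading the eight results together would take a treatment that restores role function to be one that harms it.

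The second is scale. Two printed constants, the 9 for Social Functioning and the 10 for Mental Health, do not follow from the rule printed in the same table.

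The data checks in section 11.1.3 (double entry, verification, database listings) would not obviously catch either fault. Entries would match the form; it is the form's scoring that is wrong.

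**Working it through.** **Inputs.** Item codes and formulas are all from Appendix 6. For each domain, lowest = number of items × smallest code and highest = number of items × largest code. The rule is (raw − lowest)/(highest − lowest) × 100.

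| Domain | Items | Codes | Raw range | Width | Printed formula gives | Rule gives |
| --- | --- | --- | --- | --- | --- | --- |
| Physical Functioning | 10 | 1–3 | 10–30 | 20 | 0–100 | 0–100 |
| Role-Physical | 4 | 1–2 | 4–8 | 4 | 0–100 | 0–100 |
| Bodily Pain (both items answered) | 2 | 1–6 | 2–12 | 10 | 0–100 | 0–100 |
| General Health | 5 | 1–5 | 5–25 | 20 | 0–100 | 0–100 |
| Vitality | 4 | 1–6 | 4–24 | 20 | 0–100 | 0–100 |
| Social Functioning | 2 | 1–5 | 2–10 | 8 | **0–88.9** | 0–100 |
| Role-Emotional | 3 | 1–2 | 3–6 | 3 | 0–100 | 0–100 |
| Mental Health | 5 | 1–6 | 5–30 | 25 | **0–10** | 0–100 |

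**Scale.** Social Functioning at its best: (10 − 2)/9 × 100 = 88.9. With the width of 8: (10 − 2)/8 × 100 = 100. Every value is multiplied by 8/9, so differences are about 11% too small. Mental Health at its best: (30 − 5)/25 × 10 = 10. With the rule's multiplier: (30 − 5)/25 × 100 = 100. Every value is one tenth of what the rule gives, so differences are 90% too small.

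**Direction.** The role formulas have the right width; the codes fed into them run the wrong way.

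- No problem on any item: Role-Physical (4 − 4)/4 × 100 = 0; Role-Emotional (3 − 3)/3 × 100 = 0.
- A problem on every item: Role-Physical (8 − 4)/4 × 100 = 100; Role-Emotional (6 − 3)/3 × 100 = 100.

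In the other six domains the best answer has the largest code: not limited at all = 3, no bodily pain = 6, excellent health = 5, full of pep all of the time = 6, no social interference = 5, calm all of the time = 6.

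As an example, take a patient who goes from two of the four physical role problems to none. The sheet moves from (6 − 4)/4 × 100 = 50 to 0. With items reversed (No = 2, Yes = 1) the score moves from (6 − 4)/4 × 100 = 50 to (8 − 4)/4 × 100 = 100. A gain of 50 points is recorded as a loss of 50.

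**Effect on tests.** Multiplying a domain by 8/9 or 1/10 scales the difference and its standard error alike, so the t or F statistic and its P value do not change. Reversing a role item replaces its code x by 3 − x, which turns the domain score into 100 minus the score. That keeps the size of a two-sided test and changes the sign of the effect.

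**Health Transition.** Item 2 is coded 1 (much better) to 5 (much worse) and converted by (raw − 1)/4 × 100, so much better = 0 and much worse = 100. This agrees with the general rule; higher means worse.

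**The case against.** The best case against giving this much weight has several parts.

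- *The table corrects itself.* The general rule stands above the formulas and yields the divisor of 8 and the multiplier of 100. The Mental Health figure may be no more than a dropped zero, or a character lost in reading the table. This is fair for those two constants. It does not reach the role items, because the rule says nothing about direction and the No = 1, Yes = 2 coding is the same in all seven rows under two separate stems.
- *The constants do not change significance.* That stands. Section 11.2.2 judges by P < 0.05, and within a domain those P values are unaffected. Reported means and differences are still wrong.
- *The protocol never says that higher is better.* True in words. The item codes of the other six domains fix that direction, and the two role domains are the exceptions.
- *This is a secondary indicator and can be repaired at scoring.* Also true. The primary outcome and sample size do not depend on it, and the item answers are on the form.

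A reader might infer more than the document supports. One might say that an overall SF-36 score would cancel itself out. The protocol defines no total or average, only separate domains. If all eight were averaged anyway, a fully well patient would score (4 × 100 + 0 + 0 + 88.9 + 10)/8 = 62.4 and the worst possible patient (100 + 100)/8 = 25.0, so the scale would be heavily diluted but not cancelled. One might also call Health Transition an error. It follows the general rule, is not one of the eight domains in section 8.2, and needs only a stated direction. Nor does the protocol rank any SF-36 domain as more important than another, so the point should not rest on that.

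**Conclusion.** The scoring sheet is wrong as written for four of the eight domains, in two different ways. Role-Physical and Role-Emotional are reversed over their full 0–100 range, so improvement would be reported as deterioration; this is the serious part. Social Functioning is compressed to 0–88.9 and Mental Health to 0–10, which falsifies their means and differences and makes them not comparable with other domains, while leaving within-domain P values as they were.

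The reversal rests on one inference, that all eight domains are meant to run in the same direction. The coding of the other six supports it. The Social Functioning fault rests only on the printed codes and the printed rule. The Mental Health fault rests on the printed multiplier and should be checked against the form in use. None of this touches the primary endpoint or the sample size. It needs correcting before any SF-36 result is calculated, because an analyst following the sheet would report the wrong sign for two domains of a named efficacy indicator.

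**What to change.** In Appendix 6:

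1. Score items 13–19 as Yes = 1, No = 2, or keep the printed codes and replace each by 3 minus the code before conversion. State that higher means better in all eight domains.
2. Change Social Functioning to (raw − 2)/8 × 100.
3. Confirm the Mental Health multiplier on the form in use and set it to (raw − 5)/25 × 100.
4. Report Health Transition separately, stating that higher means worse.
5. Rescore all completed sheets from the item answers, not from the domain scores written on them, since one cannot tell whether the person scoring followed the printed formulas. If the printed codes change during the trial, record which form version each sheet used, so that no item is reversed twice.

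The cost is one corrected form and a few lines of scoring syntax. At most 66 × 6 = 396 sheets need rescoring, and nothing has to be collected again.

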5.1 Sample Size Estimation

According to the research by Yang Jing-ming and his colleagues, under the conditions of β=0.1 and α=0.05, the effect size is 0.5. Pain scores will be used as the primary measurement standard, and G*Power 3.1.9.7 will be used to estimate the sample size. It is calculated that there will be approximately 54 patients in the study cohort, and considering a 10% dropout rate, each group will include 22 people, requiring a total of 66 participants for this RCT.

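### SF-36 Bodily Pain: the item 22 codes used when item 21 is blank do not fit the conversion formula, so the best possible score is 80 instead of 100

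*Protocol*

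**What the plan says.** All the relevant rules stand in the protocol's Appendix 6, Table 5.

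- Item 21 ("How much bodily pain have you had during the past 4 weeks") has six answers, coded 6/5.4/4.2/3.1/2.2/1 from none to very severe.
- Item 22 (interference of pain with work) has five answers and two rows of codes. The row "Answered items 21" is 6/4.75/3.5/2.25/1. The row "Unanswered items 21" is 5/4/3/2/1.
- The domain is defined as "Bodily Pain(BP), Consist of items 21, 22" and converted by "BP=（actual score-2）/10×100".
- For missing items, "missing entry scores are replaced by the average score of their respective aspect".
- Above the domain formulas stands a general rule: "Score conversion = (actual score - lowest score in that aspect) / (highest score in that aspect - lowest score in that aspect) × 100".

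No other divisor is given for Bodily Pain when item 21 is blank. Section 8.2 lists the SF-36 as a secondary efficacy indicator, with bodily pain as one of its eight domains. Appendix 2 schedules it at six time points.

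**The concern.** The form foresees a blank item 21 and gives item 22 its own codes for that case, but those codes cannot fill the range that the Bodily Pain formula assumes. Two patients with no pain and no interference would then receive different scores only because one of them left a box empty. Higher values mean less pain on this scale, so the error makes the patient with the blank item look worse. If blanks differ in number between the three groups or across visits, the error enters the comparisons of this domain. It does not touch the primary outcome, which is measured by the pelvic pain scale or the NIH-CPSI.

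**Working it through.** **Inputs**, all from Appendix 6, Table 5: the item 21 codes, the two item 22 rows, the Bodily Pain formula and the missing-item rule. The sample size inputs of section 5.1 play no part.

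**Step 1: reproduce the plan's formula on complete forms.** BP = (item 21 + item 22 − 2)/10 × 100.

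- Best answers: 6 + 6 = 12, so BP = (12 − 2)/10 × 100 = 100.
- Worst answers: 1 + 1 = 2, so BP = (2 − 2)/10 × 100 = 0.

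The constants 2 and 10 are thus reproduced by the item 21 codes together with the printed row for item 21 answered.

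**Step 2: item 21 blank, as printed.** Item 22, scored s, is the only answered item of the domain, so the average equals s and item 21 is set to s. The sum is 2s and BP = (2s − 2)/10 × 100.

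| Answer to item 22 | Code s (printed) | Sum 2s | BP as printed | BP with codes 6/4.75/3.5/2.25/1 | Shortfall |
|---|---|---|---|---|---|
| Not at all | 5 | 10 | 80 | 100 | 20 |
| A little bit | 4 | 8 | 60 | 75 | 15 |
| Moderately | 3 | 6 | 40 | 50 | 10 |
| Quite a bit | 2 | 4 | 20 | 25 | 5 |
| Extremely | 1 | 2 | 0 | 0 | 0 |

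The printed row gives sums from 2 to 10. The other row spreads the five answers in equal steps of 1.25 over 1 to 6; doubled, it fills 2 to 12, which is what the formula needs when item 22 stands in for item 21.

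**Step 3: other readings of the average.** Suppose the imputed value m is not the patient's own item 22 score but some other value within the item 21 codes. With s = 5, BP = (5 + m − 2)/10 × 100. For m = 6, 5.4, 4.2, 3.1, 2.2 and 1 this gives 90, 84, 72, 61, 52 and 40. No value reaches 100.

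**Step 4: the general rule in place of the printed formula.** With the range 2 to 10 that arises in step 2, (2s − 2)/8 × 100 gives 100/75/50/25/0, and the shortfall disappears.

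**Step 5: swap the two row labels and change nothing else.** With item 21 blank, BP is 100/75/50/25/0. With both items answered, the best sum is 6 + 5 = 11 and BP = (11 − 2)/10 × 100 = 90. The shortfall moves from forms with a blank item 21 to complete forms.

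**Step 6: how far a group mean could move.** The number of blanks is not given. For illustration, one form in a group of 22 that is scored 20 points too low shifts that group's mean at that visit by 20/22 = 0.9 points. The ceiling on SF-36 forms is 66 × 6 = 396.

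**The case against.** The strongest reply is that the table also states a general highest-minus-lowest rule, and that this rule removes the shortfall if the range is taken as 2 to 10 (step 4). It does not settle the matter: the table prints one explicit Bodily Pain formula with divisor 10, and whoever programs the scoring will use it. If a second divisor is meant for a blank item 21, the form has to say so.

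It can also be said that the averaging rule does not state which average is meant. That is true, and the figure of 80 rests on reading it as the patient's own answered item. Step 3 shows that other values change the figure but do not reach 100.

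A reader might infer that the two rows have simply been interchanged, since the evenly stretched row suits the case in which item 22 stands in for item 21. The form does not show this. The printed row for item 21 answered is the one that reproduces the 2 to 12 range, and a bare swap caps complete forms at 90. Nor does the document give a reason to doubt the row used for complete forms, which spans 0 to 100 as printed. To which case each row belongs can be decided only from the instrument's scoring source, which is not at hand.

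Finally, blanks should be few. Section 14.1 requires every item of the case report form to be completed, and section 14.4 assigns one researcher to carry out the SF-36 assessment. This stands, and it limits the importance of the point.

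**Conclusion.** The scoring rule for a blank item 21 is wrong as written. Under the printed formula, with the missing item set to the patient's own item 22 score, Bodily Pain can reach only 80, and the shortfall is 20, 15, 10, 5 and 0 points from the best to the worst answer. Under any other imputed value within the item 21 codes, a patient with no interference still reaches at most 90. The result assumes that the printed divisor of 10 is applied to every form.

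The point is minor: it concerns one domain of a secondary outcome and only forms on which item 21 was skipped, a number the protocol does not give and which is probably small. An interchange of the rows remains a possible explanation, not a finding.

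**What to change.** When item 21 is missing, score item 22 as 6/4.75/3.5/2.25/1. Forms with item 21 blank then span 0 to 100, and complete forms keep their scores. An alternative is to keep 5/4/3/2/1 and print a separate divisor of 8 for that case. In either case, state that the average is taken over the patient's own answered items in the domain.

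Before data entry, check both item 22 rows against the scoring source cited under the table. If the source does assign the rows the other way round, more than the labels must change, because complete forms must still be able to reach 100.

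The same check should cover the rest of the conversion table. Social Functioning divides by 9 although its two items, each scored 1 to 5, have a range of 8, and Mental Health multiplies by 10 where the general rule has 100. Those two are separate from this point and affect every form.

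The cost is one correction to the form and to the scoring syntax, with no change to data collection.
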